### Statistical methods

#### Sample size considerations

This is an observational study aimed at describing the safety, effectiveness and patient reported outcomes in patients treated with secukinumab and other indicated approved therapies for moderate to severe chronic plaque psoriasis. Given the observational nature of the study, sample size considerations are based on the precision of measuring the primary outcome measure, namely the incidence of total adverse events (AEs), total serious AEs (SAEs) and infections, as measured with the width of the 95% confidence interval (CI).

With 1250 patients in the secukinumab cohort, and assuming an incidence rate of 60% for total AEs, the 95% CI will be 60% ± 3%, or 5% of the point estimate; for SAEs, assuming an incidence of 5%, a sample size of 1250 patients will yield a 95% CI of ±1.2% or 24% of the point estimate; for infections, assuming an incidence of 30%, a sample size of 1250 patients will produce a 95% CI of ±3%, or 10% of the point estimate. All within acceptable level of precision.

Although the primary aim of the study will be to describe the incidence of AEs in the two study cohorts, between cohort comparisons may be conducted for descriptive/exploratory purposes only without any a-priori hypothesis testing. With 1250 patients per cohort, the study will be able to detect with 90% power and 5% significance, an odds ratio of 1.30 for any adverse event, an odds ratio of 1.75 for SAEs, and an odds ratio of 1.35 for infections.

Approximately 80% are planned to be recruited from Canada and 20% from the participating Latin American countries.

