**Methods:**

This is a multinational (Canadian and Latin American), prospective, observational study of adult patients with moderate to severe psoriasis that initiate treatment with secukinumab or other approved therapies as per local standard of care. A total of 2500 patients (1250 per cohort) will be recruited in the practices of hospital and community dermatologists. Decision regarding treatment must have been reached prior to and independent of patient enrollment in the study. The study includes a 5-year follow-up with recommended assessments at Baseline, 3 and 6 months post-Baseline, and every 6 months thereafter. The primary objective of the study is safety. Secondary outcome measures relate to effectiveness (Investigator’s Global Assessment -IGA mod 2011-, Psoriasis Areas and Severity Index, Body Surface Area), patient reported outcomes (Dermatology Life Quality Index, Work Productivity and Activity Impairment Questionnaire, Hospital Anxiety and Depression Scale, Psoriasis Epidemiology Screening Tool, Psoriasis Symptom Diary, and Treatment Satisfaction Questionnaire), and healthcare resource utilization.

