#### Inclusion criteria

Able to give written informed consent.At least 18 years of age at time of informed consent signature.Confirmed diagnosis of moderate to severe chronic plaque-type psoriasis diagnosed by a specialist and presence of moderate to severe psoriasis symptoms according to the physician’s clinical judgment at the time of recruitment.Patient is initiating a treatment for psoriasis as per regional policy. This may include secukinumab, other biologics, systemic treatments, and phototherapy. Decision to treat with any of the above-mentioned treatments must have been reached prior to and independently of recruitment in the study.Treatments are prescribed in accordance to the product monograph and regional regulatory and reimbursement policies.Patient is able to understand and communicate with the investigator and comply with the requirements of the study.

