### Statistical analyses

AEs and SAEs will be summarized for the two treatment cohorts using the total number of events, the total number of patients and percentage of patients who experienced at least one event within each body system and within each preferred term of the Medical Dictionary for Regulatory Activities (MedDRA); in these descriptive analyses, crossed-over patients (to either direction) will be described as a separate treatment cohort. Within each treatment cohort, patients experiencing the same event multiple times will be only counted once for the corresponding preferred term and body system. Relative risk/odds and incidence density rate ratio will be estimated to assess the difference between cohorts.

The levels of all physician-reported and patient-reported outcomes will be described for all visits by baseline treatment cohort; between-cohort differences will be assessed using the independent-samples t-test (or non-parametric alternative, as needed) for continuous variables and the chi-square test for categorical variables. In addition, the absolute changes in IGA, PASI, and BSA, will be described and the paired t-test will be conducted to assess the within-group change from baseline at each visit. Multivariate mixed models with repeated measures that may adjust for potential confounders will be used to assess the levels of each of these continuous parameters (IGA, PASI, BSA, DLQI, HADS, PEST, WPAI and PSD) over the five-year follow up period of the study.

For each visit, achievement of therapeutic endpoints, specifically IGA ≤ 1, IGA = 0, PASI 50, 75, 90 and 100 and DLQI ≤1 will be described with the proportion within each treatment cohort. Between-cohort differences will be assessed with generalized estimating equations. Time to achieving therapeutic endpoints, specifically IGA ≤ 1, IGA = 0, PASI 50, 75, 90 and 100 and DLQI ≤1, and the durability of response will be described with the Kaplan-Meier estimator. Between-cohort differences will be described with the log-rank test. Furthermore, Cox’s proportional hazards models that may adjust for potential confounders will be used to compare the two treatment cohorts.

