## Discussion

Post-approval observational studies are the only source of information that allows ongoing rigorous prospective surveillance for safety signals under routine clinical care and the assessment of real-world effectiveness, which are necessary for establishing the true population-based benefit-risk ratio of approved treatments. Furthermore, when conducted properly, observational studies play an important role in understanding, and possibly driving, the physician decision-making process in real-world, including but not limited to, treatment selection, titration, and discontinuation, as well as rationale behind these decisions. Finally, the collection of real-world healthcare resource utilization data allows the health economic evaluation of available treatment options which is not possible in controlled clinical trial settings. The extensive clinical, health-economic, and patient-reported outcomes collected, the long-term patient follow-up, and the large sample size of PURE will allow the assessment of all aforementioned objectives. Furthermore, the limited inclusion/exclusion criteria and the observation of treatment cross-overs and treatment changes per the discretion of the treating physician, will provide a valid representation on the real-world management of patients with moderate to severe chronic plaque psoriasis. Finally, an important strength of the PURE study is the use of standardised validated questionnaires which increases the internal validity of the findings and allows the comparison with other similar studies.

An important limitation of the current study, inherent in observational studies, is a high likelihood of bias by indication due to the fact that patients will be treated per the discretion of the physician. However, itself, the potential description of such a bias, is of interest given that would represent the clinical reality. In order to minimize the effect of this bias on the study results, pertaining to the comparison of the two treatment cohorts, multivariate statistical methods will be used.

In summary, PURE is a large, prospective, disease registry that will provide an accurate and comprehensive overview of the clinical reality of treating moderate to severe chronic plaque psoriasis in Canada and Latin America which may have direct implications for patients, caregivers, and healthcare providers on the management of the illness, as well as for policy makers when assessing available interventions.

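### The exploratory safety comparison is stated only as pooled ratios with no regional stratification or adjustment, although treatment access depends on country and the Discussion promises multivariate methods

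*Protocol article*

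**What the plan says.** The abstract's Methods set the recruitment target: "A total of 2500 patients (1250 per cohort) will be recruited in the practices of hospital and community dermatologists". Sample size considerations gives the geography in one sentence, for the study as a whole: "Approximately 80% are planned to be recruited from Canada and 20% from the participating Latin American countries". Nothing links the two targets.

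The cohorts are defined by the therapy started. Under Study design, the comparison cohort receives therapies approved in the patient's country. The Inclusion criteria add: "Treatments are prescribed in accordance to the product monograph and regional regulatory and reimbursement policies".

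On safety, Statistical analyses describes AEs and SAEs by cohort and then states: "Relative risk/odds and incidence density rate ratio will be estimated to assess the difference between cohorts". No covariate, stratum or model accompanies that sentence. The same section names mixed models and Cox models in which adjustment for confounders is optional. The mixed models are for the clinical and patient-reported scores, and the Cox models follow the time-to-endpoint analyses of those measures.

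Two further statements bear on the point. Sample size considerations calls between-cohort comparisons descriptive or exploratory, with no prior hypothesis test. The Discussion acknowledges bias by indication and says multivariate methods will be used to limit it in comparing the cohorts.

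**The concern.** Country can influence both sides of the safety contrast. It affects which cohort a patient can enter, through local approval and reimbursement. It may also affect the recorded event rate, through differences in AE reporting, background infection and routine care. The Discussion attributes the bias to physician discretion; access determined by country is a separate route that it does not mention.

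If the regional shares differ between cohorts and the event rates differ between regions, a crude pooled ratio departs from 1 with no treatment effect at all. Calling the comparison exploratory does not prevent this: having no formal test bears on error control, not on bias. A published relative risk for secukinumab against other therapies will be read as information about the drugs.

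The article also describes the confounding control in two ways. The Discussion makes a general commitment to multivariate methods, but the analysis section assigns none to the primary outcome domain.

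**Working it through.** **1. The plan's own precision figures.** Inputs from Sample size considerations: n = 1250, with assumed incidences of 60% (any AE), 5% (SAE) and 30% (infection). Half-width = 1.96 × √(p(1−p)/n).

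- Any AE: 1.96 × √(0.60 × 0.40/1250) = 2.72 points (stated as 3).
- SAE: 1.96 × √(0.05 × 0.95/1250) = 1.21 points (stated as 1.2).
- Infection: 1.96 × √(0.30 × 0.70/1250) = 2.54 points (stated as 3).

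These agree with the plan after rounding. For SAEs the plan says: "assuming an incidence of 5%, a sample size of 1250 patients will yield a 95% CI of ±1.2% or 24% of the point estimate"; 1.21/5 = 24%. The pooled precision statement is sound.

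**2. Can country mix alone move the safety contrast?** Assume no treatment effect. Let s be the Latin American share of a cohort, pC the Canadian incidence and pL the Latin American incidence, the same in both cohorts. Then

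cohort incidence = (1 − s) × pC + s × pL.

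Take pC = 60%, the plan's any-AE figure. Two inputs are assumptions, because the article gives neither: pL is 0.5 to 0.8 times pC (30% to 48%), and the shares are 10% vs 30% or 15% vs 25%. Both pairs average 20% over equal cohorts, so both satisfy the stated overall split.

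| Latin American shares | pL | Cohort incidences | Difference (points) | Spurious OR |
|---|---|---|---|---|
| 20% vs 20% | any | equal | 0 | 1.00 |
| 15% vs 25% | 48% | 58.2% vs 57.0% | 1.2 | 1.05 |
| 15% vs 25% | 30% | 55.5% vs 52.5% | 3.0 | 1.13 |
| 10% vs 30% | 48% | 58.8% vs 56.4% | 2.4 | 1.10 |
| 10% vs 30% | 30% | 57.0% vs 51.0% | 6.0 | 1.27 |

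For the last row: (0.57/0.43)/(0.51/0.49) = 1.326/1.041 = 1.27.

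For 10% vs 30% and the same rate ratios, the spurious OR is 1.06 to 1.17 for infections and 1.05 to 1.12 for SAEs. The direction is not fixed either: if Latin American any-AE incidence were 1.25 times the Canadian (75%), shares of 10% vs 30% would give 0.88.

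For scale, the plan says it can detect an any-AE OR of 1.30 with 90% power. The top of the illustrated range comes close to that; the milder cases do not.

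**3. Does stratifying by region remove it?** In the last row, Canadian incidence is 60% in both cohorts and Latin American incidence is 30% in both. Each stratum-specific OR is 1.00, so the Mantel-Haenszel OR is 1.00 whatever the shares.

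**4. What region-specific reporting would look like.** If 80/20 happened to hold within a cohort, it would contain 0.20 × 1250 = 250 Latin American and 1000 Canadian patients. With the same incidences and formula:

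- Latin America: ±6.1 (any AE), ±2.7 (SAE), ±5.7 (infection) points.
- Canada: ±3.0, ±1.35, ±2.8 points.

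**The case against.** The strongest reply is that this is a condensed article. Covariate lists and regional tables usually sit in the full protocol or analysis plan, and silence is not a decision to leave the contrast unadjusted. The primary aim is description, the contrast is exploratory, and the Discussion already commits to multivariate methods. The bias figures also rest on regional rates and shares that no document supplies, and no passage shows that access to secukinumab actually differed between the countries.

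Much of this stands. It limits the size and weight of the point, and no one should read the article as ruling out adjustment. What remains is that the article does describe adjustment models, allocates them to effectiveness and patient-reported outcomes, and gives the primary safety outcomes only ratios. That does not fit the Discussion's general promise.

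Three stronger conclusions are tempting and are not supported.

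- **That the stated precision is wrong for Latin America.** The half-widths are given for 1250 patients and reproduce. The Discussion's closing claim that the registry "will provide an accurate and comprehensive overview of the clinical reality of treating moderate to severe chronic plaque psoriasis in Canada and Latin America" is a general statement, not a promise of regional precision. At one fifth of the sample an interval is √5 = 2.24 times wider; that is true of any such subgroup and is not an error.
- **That the 80/20 split must be enforced within each cohort.** A quota would restrict enrolment in an observational registry, and analysis can handle an unequal mix.
- **That some countries or periods should be left out of the contrast.** This presumes access differences that the documents do not show.

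**Conclusion.** The point holds in a limited form. The analysis section names no stratified or adjusted method for the between-cohort safety comparison, the Discussion says multivariate methods will be used for the cohort comparison, and the entry rules tie available treatment to country. A crude pooled ratio can therefore carry a country-mix bias.

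Its size is unknown. Under the assumptions shown (Latin American any-AE incidence 0.5 to 0.8 times the Canadian, shares of 15% vs 25% or 10% vs 30%), the spurious any-AE OR is about 1.05 to 1.27. It is exactly 1.00 if shares are equal or if regional incidences do not differ. The contrast is exploratory, and the within-cohort incidences and their pooled intervals remain valid descriptions of the patients enrolled. This is a modest correction to the analysis text, not a flaw in the design or the sample size.

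**What to change.** In Statistical analyses:

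- Estimate the safety relative risk or odds ratio and the incidence density rate ratio stratified by region (for example Mantel-Haenszel, Canada vs Latin America), or adjusted for region or country, and report them beside the crude ratios.
- Include region or country in the mixed, GEE and Cox models.
- Tabulate region by cohort, with region-specific incidence of AEs, SAEs and infections and their 95% confidence intervals.

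This would bring the safety analysis into line with the Discussion. If the full protocol or analysis plan already provides for it, a sentence in the article saying so is enough.

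The cost is wording and a little more analysis, with no extra patients or data. The Latin American intervals will be wide, at about ±6.1, ±2.7 and ±5.7 points with some 250 patients per cohort, and should be presented as descriptive. Recruitment targets and the stated precision figures need no change.

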### Statistical analyses

AEs and SAEs will be summarized for the two treatment cohorts using the total number of events, the total number of patients and percentage of patients who experienced at least one event within each body system and within each preferred term of the Medical Dictionary for Regulatory Activities (MedDRA); in these descriptive analyses, crossed-over patients (to either direction) will be described as a separate treatment cohort. Within each treatment cohort, patients experiencing the same event multiple times will be only counted once for the corresponding preferred term and body system. Relative risk/odds and incidence density rate ratio will be estimated to assess the difference between cohorts.

The levels of all physician-reported and patient-reported outcomes will be described for all visits by baseline treatment cohort; between-cohort differences will be assessed using the independent-samples t-test (or non-parametric alternative, as needed) for continuous variables and the chi-square test for categorical variables. In addition, the absolute changes in IGA, PASI, and BSA, will be described and the paired t-test will be conducted to assess the within-group change from baseline at each visit. Multivariate mixed models with repeated measures that may adjust for potential confounders will be used to assess the levels of each of these continuous parameters (IGA, PASI, BSA, DLQI, HADS, PEST, WPAI and PSD) over the five-year follow up period of the study.

For each visit, achievement of therapeutic endpoints, specifically IGA ≤ 1, IGA = 0, PASI 50, 75, 90 and 100 and DLQI ≤1 will be described with the proportion within each treatment cohort. Between-cohort differences will be assessed with generalized estimating equations. Time to achieving therapeutic endpoints, specifically IGA ≤ 1, IGA = 0, PASI 50, 75, 90 and 100 and DLQI ≤1, and the durability of response will be described with the Kaplan-Meier estimator. Between-cohort differences will be described with the log-rank test. Furthermore, Cox’s proportional hazards models that may adjust for potential confounders will be used to compare the two treatment cohorts.

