### Study design

PURE is a multinational, prospective, observational cohort study conducted in the practices of hospital and community dermatologists in Canada and Latin America (Argentina, Brazil, Costa Rica, Guatemala, Mexico, Panama) that treat patients with moderate to severe chronic plaque psoriasis. [14] Patients with moderate to severe chronic plaque psoriasis whom, prior to and independent of study enrollment, the treating physician has decided to treat with an indicated approved regimen as per standard of care in each participating country.

Patients are followed for up to 5 years from the time of enrollment. In accordance with the observational nature of the study, no assessment visits are imposed for the exclusive purpose of the study, however follow-up visits are recommended at 3 and 6 months post-baseline and every 6 months thereafter. Furthermore, any changes in the management of the patient including, but not limited to, changes in medication dose or frequency, termination of a medication or initiation of a new treatment is at the sole discretion of the treating physician and is to be recorded in the study data collection forms. At any time, patients may be withdrawn from the study by the treating physician or on the patient’s expressed choice.

There are two distinct patient cohorts in the study, those that initiate treatment with secukinumab and those that initiate treatment with other indicated and country-approved therapies as per local standard of care. Given the longitudinal nature of the study, it is anticipated that treatment cohort cross-over can occur. All patients will be followed in the study regardless of and after treatment cross-over, as long as they continue to fulfill the study inclusion and exclusion criteria. All analyses will be based on the intent-to-treat (ITT) principle even though treatment cohort may be considered as a time-dependent variable in some analyses.

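### Placing crossed-over patients in a separate cohort defines the adverse event cohorts by a post-baseline event, conflicts with the ITT statement, and biases the safety estimates if switching is related to adverse events

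*Protocol article*

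**What the plan says.** The Study design section of the protocol article defines two cohorts: "those that initiate treatment with secukinumab and those that initiate treatment with other indicated and country-approved therapies as per local standard of care". It expects patients to move between them ("it is anticipated that treatment cohort cross-over can occur"), follows everyone for up to five years regardless of cross-over, and states that "All analyses will be based on the intent-to-treat (ITT) principle", while allowing treatment to be time-dependent in some analyses.

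The Statistical analyses section sets a different grouping for the descriptive AE and serious AE (SAE) tables: "crossed-over patients (to either direction) will be described as a separate treatment cohort". The same paragraph ends: "Relative risk/odds and incidence density rate ratio will be estimated to assess the difference between cohorts". The next paragraph groups physician- and patient-reported outcomes by baseline cohort. The AE paragraph does not.

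The Outcome variables section makes total AEs, SAEs and infections the primary outcome. It adds a third scheme, under which AEs are mapped to an exposure by a hierarchy with secukinumab at the top.

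**The concern.** The rule moves patients, not person-time. Whether a patient counts in the secukinumab cohort depends on whether that patient later switches, and the text provides no split at the switch date that would leave earlier events with the earlier drug. Patients who change therapy because of an AE are among the most informative for a safety profile, and they would leave the cohort in which the event arose.

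The cohorts do not lose patients in the same way. One is a single drug. The other pools all other approved therapies, and the Inclusion criteria say of the treatments started: "This may include secukinumab, other biologics, systemic treatments, and phototherapy". Every secukinumab patient who changes to another therapy is a cross-over. A comparator patient who moves from one non-secukinumab therapy to another is not, and stays. The third group mixes both directions of switch, so it describes no single treatment.

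At stake are the descriptive AE and SAE incidence for secukinumab, which is the primary output, and the exploratory relative risk, odds ratio (OR) and rate ratio.

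**Working it through.** **1. The groupings side by side.** Take a patient who starts secukinumab, has an AE, and then changes to another biologic.
- Study design (ITT): the event counts in the secukinumab cohort.
- Statistical analyses: the patient is in the crossed-over cohort.
- Outcome variables: the event is mapped by an exposure hierarchy, whose relation to either grouping is not stated.

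A patient-level cohort defined by later switching is neither ITT nor a time-dependent treatment variable.

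**2. The plan's own precision figures** (Sample size considerations, n = 1250). The half-width is 1.96 × √[p(1−p)/n].
- Any AE, p = 0.60: 2.72% (stated ±3%)
- SAE, p = 0.05: 1.21% (stated ±1.2%)
- Infections, p = 0.30: 2.54% (stated ±3%)

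These reproduce after rounding.

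**3. Effect on the secukinumab incidence.** Let a be the probability of switching given an event and b the probability without one. Both are assumptions, since the article gives no rates. The incidence among patients who remain is p(1−a) / [p(1−a) + (1−p)(1−b)]. With a = 0.30 and b = 0.10:
- Any AE: 0.42/(0.42 + 0.36) = 53.8% instead of 60%; 0.78 × 1250 = 975 patients remain.
- SAE (same rates by SAE status): 0.035/(0.035 + 0.855) = 3.9% instead of 5%; about 1112 remain.
- Infections (same rates by infection status, and assuming they are summarised under the same rule): 0.21/(0.21 + 0.63) = 25% instead of 30%; 1050 remain.

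**4. Effect on the odds ratio when there is no true difference.** Let c be the share of comparator switches that go to secukinumab, with a and b equal in both cohorts. The odds in the secukinumab cohort are multiplied by (1−a)/(1−b), and in the comparator by (1−ca)/(1−cb). The apparent OR is the ratio of these factors and does not depend on p.

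For a = 0.30, b = 0.10, c = 1/3: (0.70/0.90)/(0.90/0.967) = 0.778/0.931 = 0.84.

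| a | b | c | apparent OR |
|---|---|---|---|
| 0.20 | 0.20 | 0.5 | 1.00 |
| 0.30 | 0.10 | 1 | 1.00 |
| 0.30 | 0.20 | 0.5 | 0.93 |
| 0.40 | 0.20 | 0.5 | 0.84 |
| 0.40 | 0.10 | 1/3 | 0.74 |
| 0.50 | 0.20 | 0.5 | 0.75 |
| 0.50 | 0.20 | 0.25 | 0.68 |
| 0.20 | 0.30 | 0.5 | 1.08 |
| 0.20 | 0.30 | 0.25 | 1.11 |

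**5. Rates over time.** A five-year simulation used exponential event times with 60% any-AE incidence, a switching hazard of 0.06 per year that triples after an AE, and c = 0.5. It gave an OR of about 0.82 and a first-event rate ratio of about 0.86 under a true null. With no link between AEs and switching, both were about 1.00.

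**6. Precision after removal**, with a = 0.30 and b = 0.10: about ±3.1% for any AE (n = 975), ±1.1% for SAEs (n about 1112) and ±2.6% for infections (n = 1050). Against the stated ±3%, ±1.2% and ±3%, this is essentially unchanged.

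**The case against.** **The rule may cover only the tables.** It is introduced as applying to the descriptive analyses, and the ratios could be meant for baseline cohorts. That reading is possible, but nothing in the paragraph restores baseline cohorts for the ratios. The tables are themselves the primary description of AE incidence, so the distortion in step 3 would remain.

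**Comparisons are exploratory.** This stands. Sample size considerations allows between-cohort comparisons only for descriptive or exploratory purposes, without prior hypotheses. A reader might speak of a biased primary safety comparison, but the article has none. The accurate wording is a comparison on the primary safety outcome.

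**The direction is not fixed.** This also stands. A reader might infer that the rule favours secukinumab by construction. The construction gives only the asymmetry. The sign depends on how AEs relate to switching, and switching for lack of effect by AE-free patients would push the OR above 1. The exposure hierarchy, with secukinumab first, could also draw events towards secukinumab, and its interaction with the crossed-over cohort is unstated.

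**The rates are assumed.** True. The OR of 0.84 in the main illustration is also nearer to 1 than the inverse of the 1.30 that the article calls detectable (1/1.30 = 0.77).

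**Loss of sample size.** A reader might argue that shrinking the cohorts undermines the planned precision. Step 6 shows that it does not.

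**Switchers are of interest in a registry.** They are, and describing them separately is legitimate as an addition. It should not decide who counts in the two main cohorts.

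**Conclusion.** The point holds. For the primary safety outcome, cohort membership in the AE and SAE summaries is set by a post-baseline event. That contradicts the ITT statement in Study design and is not reconciled with the exposure hierarchy in Outcome variables. The conflict lies in the text itself, so it is more than a detail left to an analysis plan.

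The size is conditional. If AEs prompt switching at the illustrative 30% against 10%, the any-AE incidence for secukinumab is understated by about 6 points, roughly twice the planned half-width. The SAE incidence is understated by about 1 point, close to its planned half-width. With one third of comparator switches going to secukinumab, no true difference appears as an OR of about 0.84, and a true OR of 1.30 as about 1.30 × 0.84 = 1.09. Over the assumptions tried, a true null gives ORs from 0.68 to 1.11. The incidence is undistorted if switching is unrelated to AEs. The OR is also unbiased if both cohorts lose switchers equally.

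**What to change.** 1. Make the main AE, SAE and infection summaries, and the relative risk and odds ratio, by initiating cohort with every patient kept. A true null then gives an OR of 1.00 as far as this selection is concerned; confounding by indication remains a separate matter.
2. For the incidence density rates, add an exposure-based analysis. Split each patient's person-time at the switch date and assign events and time to the therapy in use, with a prespecified risk window, so that events before the switch stay with the earlier therapy.
3. Keep the crossed-over group only as a supplementary description, shown by direction of switch and with events before and after the switch separated.
4. Reconcile the Study design, Outcome variables and Statistical analyses sections, stating which grouping feeds each table and ratio and where the exposure hierarchy applies.

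The cost is wording and some extra programming. Study design already requires treatment changes to be recorded, so no new data are needed.
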